# Integrated Sustainable childhood Pneumonia and Infectious disease Reduction in Nigeria (INSPIRING) through whole system strengthening in Jigawa, Nigeria: study protocol for a cluster randomised controlled trial

**DOI:** 10.1186/s13063-021-05859-5

**Published:** 2022-01-31

**Keywords:** Child mortality, Cluster randomised controlled trial, Participatory learning and action, Community, Pneumonia, Nigeria

## Abstract

**Background:**

Child mortality remains unacceptably high, with Northern Nigeria reporting some of the highest rates globally (e.g. 192/1000 live births in Jigawa State). Coverage of key protect and prevent interventions, such as vaccination and clean cooking fuel use, is low. Additionally, knowledge, care-seeking and health system factors are poor. Therefore, a whole systems approach is needed for sustainable reductions in child mortality.

**Methods:**

This is a cluster randomised controlled trial, with integrated process and economic evaluations, conducted from January 2021 to September 2022. The trial will be conducted in Kiyawa Local Government Area, Jigawa State, Nigeria, with an estimated population of 230,000. Clusters are defined as primary government health facility catchment areas (*n* = 33). The 33 clusters will be randomly allocated (1:1) in a public ceremony, and 32 clusters included in the impact evaluation.

The trial will evaluate a locally adapted ‘whole systems strengthening’ package of three evidence-based methods: community men’s and women’s groups, Partnership Defined Quality Scorecard and healthcare worker training, mentorship and provision of basic essential equipment and commodities. The primary outcome is mortality of children aged 7 days to 59 months. Mortality will be recorded prospectively using a cohort design, and secondary outcomes measured through baseline and endline cross-sectional surveys.

Assuming the following, we will have a minimum detectable effect size of 30%: (a) baseline mortality of 100 per 1000 livebirths, (b) 4480 compounds with 3 eligible children per compound, (c) 80% power, (d) 5% significance, (e) intra-cluster correlation of 0.007 and (f) coefficient of variance of cluster size of 0.74. Analysis will be by intention-to-treat, comparing intervention and control clusters, adjusting for compound and trial clustering.

**Discussion:**

This study will provide robust evidence of the effectiveness and cost-effectiveness of community-based participatory learning and action, with integrated health system strengthening and accountability mechanisms, to reduce child mortality. The ethnographic process evaluation will allow for a rich understanding of how the intervention works in this context. However, we encountered a key challenge in calculating the sample size, given the lack of timely and reliable mortality data and the uncertain impacts of the COVID-19 pandemic.

**Trial registration:**

ISRCTN 39213655. Registered on 11 December 2019

**Supplementary Information:**

The online version contains supplementary material available at 10.1186/s13063-021-05859-5.

## Background

Pneumonia remains the leading cause of infectious childhood deaths, with half of these deaths occurring in just 5 countries, one of which is Nigeria [1]. Northern Nigerian states account for six of the top 10 respiratory mortality hotspots in Africa, including Jigawa State [2]. However, high-quality data on pneumonia incidence, case fatality rates and the point prevalence of different pneumonia severity classifications are lacking [3]. An exploration of drivers for the high pneumonia morbidity and mortality burden in this setting found low coverage of protective and preventive factors (e.g. vaccine coverage and clean cooking) [3] and multiple misconceptions [4]. Diverse stakeholders prioritised the strengthening of primary care and community knowledge to tackle pneumonia in the context of Jigawa State [5].

Several community-based participatory empowerment approaches for improving maternal, neonatal and child health outcomes have been trialled. Those which encourage collective critical consciousness and problem solving have been effective in reducing maternal and neonatal mortality [6] and more recently in reducing diabetes [7]. Participatory Learning and Action (PLA) cycles have been adapted in several cultural contexts and are recommended by the World Health Organization (WHO) as an approach to mobilising community participation in health [8].

In parallel, increasing knowledge and awareness of pneumonia needs to be met with the ability to supply high-quality healthcare services. Issues with equipment, supplies and healthcare worker knowledge of diagnosing and treating children according to WHO’s Integrated Management of Childhood Illnesses (IMCI) guidelines were seen in Jigawa [9]. Maintaining standards of care, particularly at primary care levels, where the majority of cases present and staff have less training, is challenging. Quality improvement interventions which consider health worker motivation, supportive supervision and accountability mechanisms are needed [10]. As with the community, such problem-solving interventions go beyond passive training to facilitate, motivate and empower health workers toward improved practice. The WHO has highlighted the importance of the interface between health systems and the communities they serve, focussing on the need for shared spaces to develop and enable people-centred services [11].

The root causes of a high paediatric pneumonia burden in Jigawa are complex and multi-faceted, spanning individual, community and health system factors. Therefore, interventions to improve illness recognition, care-seeking, care provision and subsequent outcomes need to take a whole systems perspective. The aim of the ‘Integrated Sustainable childhood Pneumonia and Infectious disease Reduction in Nigeria’ (INSPIRING) trial is to evaluate if a complex intervention of community groups linked to primary care and health system strengthening will reduce child mortality and improve child health, in Jigawa State.

## Methods

The INSPIRING Jigawa Trial is a cluster randomised controlled trial (cRCT), evaluating a three-part whole system strengthening intervention package, in Kiyawa Local Government Area (LGA), Jigawa State, Nigeria. This will be complemented with an embedded ethnographic process evaluation and economic evaluation to determine cost-effectiveness. The trial will run from January 2021 to September 2022, following a formative phase and COVID-19 adaptation from December 2019 to December 2020 (Fig. 1). The primary research question and secondary process and economic evaluation research questions are detailed in Table 1.

**Fig. 1 Fig1:**
[figure not shown]
SPIRIT trial schematic

**Table 1 Tab1:** Impact, process and economic evaluation research questions

Impact evaluation *(primary research question)*	What is the impact of a package of gender-sensitive group-based problem-solving interventions at community and community-facility levels to improve protection, prevention, diagnosis and treatment of childhood pneumonia and infectious diseases on mortality of children under-5 years old in Kiyawa LGA, Nigeria?
**Process evaluation**	Which attributes, mechanisms, effects (intended and unintended) and contextual factors enable or prevent gender-sensitive group-based problem-solving interventions at community and community-facility levels to improve protection, prevention, diagnosis and treatment of childhood pneumonia and infectious diseases in Kiyawa LGA?
	How do various stakeholders understand their role in the process of childhood pneumonia prevention in Jigawa, and how does this perception shift through participation in community-level interventions?
	How do social norms around gender, participation and decision-making in the home shape participation and engagement in community-level interventions to tackle childhood pneumonia?
	How do power and social dynamics and relationships in the wider community shape channels of communication between families and practitioners, and how does this impact on the ability to implement and efficacy of community-facility referral pathways?
	Was the intervention delivered (including fidelity, dose, reach, intensity, adaptation and duration) as intended?
**Economic evaluation**	What is the cost per disability-adjusted life-year (DALY) averted of a package of group-based problem-solving interventions at community and community-facility levels to improve protection, prevention, diagnosis and treatment of childhood pneumonia and infectious diseases in Jigawa State, Nigeria?
	Is it cost-effective considering opportunity costs of current and projected health spending (i.e. what is the estimated net benefit of the intervention package)?
	If the intervention package is cost-effective, is it affordable given the budget required for scale-up in Jigawa State, Nigeria?

### Setting

The trial will be conducted in Kiyawa LGA, Jigawa State. The population is approximately 230,000 people, with 25% estimated to be children under-five years. The area is predominantly Islamic with two main ethnic groups—Hausa and Fulani, living in mostly rural communities [12]. At study inception, Kiyawa LGA had 33 government health facilities, made up of primary health centres (PHCs), basic health centres and health posts, and a further two private primary care facilities and private pharmacy shops. Children who meet WHO criteria for referral should be sent to PHCs or hospital care at Dutse General or Rasheed Shekoni Teaching hospital, both located in the state capital, Dutse, in the neighbouring LGA (Fig. 2). Maternal and child health services are provided free at selected facilities, but out-of-pocket costs still pose a financial barrier to access [4]. Kiyawa LGA was selected through discussion between Save the Children Nigeria, the State Ministry of Health (SMOH) and the Jigawa State Government, using pre-defined criteria (e.g. mortality burden, road access).

**Fig. 2 Fig2:**
[figure not shown]
Map of Kiyawa LGA with study clusters

### Design

This is a pragmatic community-based cRCT, following a formative phase of intervention development, concept testing and community engagement. Impact against the primary outcome will be evaluated using an open prospective cohort, recording vital events (pregnancies, births and under-five child deaths) amongst a random sample of women on a rolling 4-monthly basis. Secondary outcomes will be recorded during cross-sectional surveys conducted at baseline (January–March 2021) and end line (July–September 2022) (Fig. 1). The same random sample of compounds, and all eligible women and children residing in these compounds, will be included in both surveys and prospective cohort.

Clusters are defined as the geographical catchment area of the 33 government primary care facilities. Clusters range in population size from approximately 1680 to 24,200 (median 5840). All villages in Kiyawa LGA will be included in the study (*n* = 425 enumerated villages); however, the Kiyawa PHC cluster will be excluded from the impact evaluation as this facility is in a peri-urban area and provides a level of inpatient care—unlike the other primary facilities. Villages are made up of compounds, which are defined as the group of structures (including ‘households’) where extended families live and have shared resources.

### Population

The target population for the impact evaluation is women of childbearing age, defined as 16–49 years inclusive, and children aged 0–59 months inclusive, who reside permanently in Kiyawa LGA. Women and children will be considered lost to follow-up if they migrate, are temporarily unavailable, or consent is withdrawn. Children of women who are lost to follow-up, or die during the study period, will still be included if they continue to reside in the same compound and an eligible caregiver can provide consent. The intervention is open to all community members, with no age or gender restrictions.

### Intervention

The intervention is a locally adapted ‘whole systems strengthening’ package of three evidence-based activities: PLA men’s and women’s groups [8], Partnership Defined Quality Scorecard (PDQS) [13–15] and training, mentorship and provision of basic essential equipment and commodities for child health (Table 1). The details of the community groups and PDQS have been refined through a co-design process, using a modified version of the community conversation methodology. In its original form, the approach has been used across a range of settings in Africa to shift and influence behaviour change in relation to health, including HIV/AIDS [16] and female genital mutilation [17]. Though typically applied as an intervention itself, our reformulation was designed to deepen engagement with communities at scale as part of the concept testing process. Conversations were organised in a similar manner to the PLA groups that will form one component of the intervention, providing an additional layer for exploring the acceptability of this approach prior to implementation. Groups of stakeholders, including men, women and healthcare workers, were brought together through a series of iterative and interactive discussions to explore perceptions of key concepts underpinning the interventions (e.g. challenges related to child health), community relationships with healthcare workers and how key intervention components would work best in their communities, including location and timing for delivery of groups and incentives. Full details of this methodology and results will be published separately.

#### PLA groups with integrated PDQS

Groups of approximately 20–30 men and women in each community will be convened. Group meetings will be held separately for men and women to allow gender norms to be respected, and tailor meetings to different locations and times. Groups are open to all community members, and sharing of group messages will be encouraged; men and women with young children and those currently pregnant will be particularly encouraged to join.

The groups will work through a four-phase PLA cycle, following an initial introductory session. The phases include the analysis of the situation and prioritisation of child health issues in their communities (phase 1), planning actions to tackle these issues (phase 2), implementing the selected strategies (phase 3) and collective self-evaluation (phase 4) (Fig. 3). The PDQS process focussed specifically on healthcare service quality issues, with group members and healthcare workers joining together to mutually agree on quality indicators and joint actions. PDQS will be incorporated into all 4 phases of the PLA cycle, where healthcare workers will attend men’s and women’s groups. Each phase can involve multiple physical meetings, decided on by group members (see the “Ethical considerations” section for details on COVID-19 mitigations). The completion of one PLA cycle is anticipated to take 4–5 months, and groups will repeat the cycle multiple times over the 18-month intervention period.

**Fig. 3 Fig3:**
[figure not shown]
Women’s and men’s group PLA cycle

We plan 340 groups to ensure the recommended coverage of one group per 500 population [6]. Groups will be led by 170 trained community health volunteers (CHVs), provided with a stipend. CHVs will facilitate an average of two groups, with 12 to 28 groups per cluster, depending on the population. CHVs will be recruited from the local communities, meeting the following criteria: previous experience in community mobilisation, basic knowledge of child health, fluent in Hausa, minimum basic primary education and resident in Kiyawa LGA. Where possible, facilitators will be recruited from those working as Volunteer Community Mobilizers (VCM), Team Supervisors or other community health workers. They will receive a 5-day training, covering the PLA approach, their roles and responsibilities, participatory skills development using observation and feedback, use of the flipbook job aid and collaboration with key community stakeholders. Following training, a questionnaire assessment will be administered, and only those showing adequate competencies in networking, negotiation and mediation, and basic child health knowledge will be retained. CHVs will be supervised by Save the Children study staff based in Dutse, in collaboration with the SMOH, Kiyawa LGA staff and health facility staff.

#### Health system strengthening

The staff at health posts, basic health centres and PHCs within the intervention clusters will receive a package of trainings to support child health, including iCCM for community health workers, IMCI for facility staff, nutrition management and vaccination supply chain management (Table 2). Training will be delivered at the start of the intervention period and then followed up with mentorship and supervision. Training and supervision will be delivered by Save the Children Nigeria in collaboration with the SMOH. A post-training ‘start-up kit’ will be provided, including basic essential equipment (e.g. respiratory rate timers, thermometers, MUAC tape) and guideline booklets and charts.

**Table 2 Tab2:** Description of health system strengthening components

Training	Participants	Training structure	Trainers	On-going support	Donated supplies and equipment
Integrated Community Case Management (iCCM) [18]	3 staff from the 17 intervention facilities, including junior CHEWs and CHIPS volunteers	6-day training, including classroom (presentations and clinical scenarios) and clinical practice sessions	Certified iCCM trainer	6-weekly* supervision visits by training facilitators and Save the Children staff	Training modules and M&E tools Job aids and chart booklets Start-up kit, including RR timer, ORS + zinc, paediatric ambu bag, MUAC tapes, thermometer
Integrated Management of Childhood Illness (IMCI) [19]	50 staff from 17 intervention facilities, including CHEWs, CHOs, nurses and doctors	6-day training, including classroom (presentations and clinical scenarios) and clinical practice sessions	Certified IMCI trainer		
Immunisation “Reaching Every District”	40 staff from 17 intervention facilities, including CHEWs, CHOs, nurses and doctors	2–3-day training, covering management, planning, data, supervision, engagement and outreach services	Certified Immunisation trainer	Financial and logistics outreach support	Vaccine carrier bags 3 electric and 2 solar refrigerators M&E tools, charts and guidelines
Nutrition–Infant and Young Child Feeding (IYCF)	50 CHO, junior CHEWs and CHEWs, and nutrition focal persons	3-day training, including classroom and practical learning	State Ministry of Health	Provision of IYCF corner, supporting food demonstrations, and supportive supervision.	Training modules and M&E tools Job aids and chart booklets MUAC tapes Plumpy nut
Pulse oximetry and oxygen therapy	25 staff at 2 referral hospitals 6 staff at 3 PHCs including CHEWs, CHOs, nurses and doctors	3-day training, including classroom and practical learning	Oxygen for Life Initiative	Annual biomedical engineer equipment audit Bi-monthly* mentorship visits by Save the Children staff	12 Lifebox pulse oximeters with universal and paediatric clip probes 8 oxygen concentrators 40 oxygen cylinders

*This schedule applies to the first 6 months post-training, after which the supervision and mentorship plan will be reviewed

*CHEW* community health extension worker, *CHO* community health officer, *CHIPS* Community Health Influencers Promoters and Services, *RR* respiratory rate, *ORS* oral rehydration salt, *MUAC* mid-upper arm circumference, *PHC* primary health centre

### Control

All clusters, including control, will have access to a child health radio programme throughout the project period (Fig. 1). The radio programme consists of weekly dramas, covering prevention, recognition and care-seeking for common childhood diseases, including pneumonia. There will be a monthly call-in session, where members of the public can ask questions and share experiences. The radio station is accessible across the whole study area.

The two referral hospitals located in Dutse LGA (Fig. 2), and three PHCs in Kiyawa LGA will be supported with oxygen and pulse oximetry, to ensure minimum standard of care is available for children meeting WHO IMCI referral criteria in intervention and control clusters.

### Outcome

The primary outcome is under-five mortality. This is defined as the number of children aged 7 days to 59 months reported to have died over a 12-month period who resided in sampled compounds (numerator), divided by the total number of children aged 7 days to 59 months who reside in sampled compounds (denominator). Deaths in the first week of life are excluded due to the challenges of accurate reporting of stillbirths and early neonatal deaths [20], and we do not expect the intervention to impact perinatal causes. Secondary outcomes are detailed in Table 3 and are based on the INSPIRING Programme Theory of Change.

**Table 3 Tab3:** Primary and secondary outcomes

Primary outcome	Definition
Under-five mortality rate	The number of confirmed* deaths amongst children aged 7 days–59 months, per 1000 livebirths reported by women in the cohort, in the last 12 months
**Secondary outcomes**	
Suspected pneumonia mortality rate	The number of confirmed* deaths classified by InterVA-5 as primarily attributable to acute respiratory infections amongst children aged 7 days–59 months, per 1000 livebirths reported by women in the cohort, in the last 12 months [21]
Pneumonia point prevalence	The proportion of children clinically assessed on the day of the survey who meet 2014 WHO IMCI definition for pneumonia or severe pneumonia, including hypoxemia [22, 46]
Women’s wellbeing	The mean Short Warwick-Edinburgh Mental Wellbeing Scale score amongst women aged 16–49 years [23]
*Treat*	
Knowledge of pneumonia	The proportion of women aged 16–49 who can name both fast and difficulty breathing as signs of pneumonia
Care-seeking for childhood illnesses	The proportion of caregivers who self-reported visiting a formal healthcare provider (including primary, secondary, private or government facilities) within 48 h of illness recognition, amongst those who reported their child has been sick in the previous 2 weeks
*Protect*	
Exclusive breastfeeding	The proportion of children aged 0–6 months whose caregiver self-reports exclusively breastfeeding
Vitamin A	The proportion of children aged 18–59 months with 2 doses of vitamin A
*Prevent*	
Vaccine coverage	The proportion of children aged 18–59 months with complete vaccine coverage according to the Nigerian Childhood Vaccination programme [24]**
Handwashing with soap	The proportion of households who self-report access to soap and water in their home for handwashing
Household air pollution	The proportion of households who self-report cooking indoors with wood/charcoal or dried grass

*Deaths which are verified by a field supervisor during a verbal autopsy visit

**Includes 1 dose BCG, 4 doses oral polio vaccine, 2 doses rotavirus vaccine, 3 doses DPT-Penta, 3 doses PCV-10 and 2 doses measles

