### Analysis

The primary analysis will be intention-to-treat, comparing under-five mortality between intervention and control clusters over a 12-month period (July 2021–June 2022), using mixed-effects logistic regression, with fixed effects for the trial arm (intervention or control), and random effects to adjust for compound-level clustering and trial cluster. Data from the first 6 months of intervention implementation (January–June 2021) will be considered as a baseline period, before any intervention effect would be expected. Any imbalances in baseline characteristics between arms will be presented to the Trial Steering Committee (TSC), who will advise on whether the primary analysis should be adjusted for these. We will conduct a complete case analysis, where only children with confirmed survival outcomes will be included; a sensitivity analysis using multiple imputation will be done, if outcome data is found to be missing at random.

Secondary analyses, using the same mixed-effects model approach, will explore differences in pneumonia prevalence, coverage of prevent and protect indicators, knowledge and care-seeking between intervention and control clusters (Table 3). Changes in pneumonia prevalence, knowledge and care-seeking between baseline and endline surveys will be described and compared using chi-squared tests.

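### At endline, most children counted for vaccine coverage (18–59 months) had passed 18 months before any effect was expected, so the difference between arms is attenuated

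*Protocol article*

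**What the plan says.** - **Outcome (Table 3, Prevent).** Vaccine coverage is "The proportion of children aged 18–59 months with complete vaccine coverage" under the national programme. The footnote lists what counts: "Includes 1 dose BCG, 4 doses oral polio vaccine, 2 doses rotavirus vaccine, 3 doses DPT-Penta, 3 doses PCV-10 and 2 doses measles". These are 15 doses. The ages at which they are due are not given.
- **Timing (Design).** Secondary outcomes come from cross-sectional surveys in January–March 2021 and July–September 2022.
- **Onset of effect (Analysis).** In the paragraph on the mortality analysis, January–June 2021 is treated as baseline, "before any intervention effect would be expected".
- **Comparison (Analysis).** The arms are compared on the prevent and protect indicators with the same mixed-effects approach as the primary outcome. No restriction by birth date or exposure is stated.
- **Package (Table 2).** The immunisation component has training, refrigerators, vaccine carriers and support for outreach. Nothing is said for or against catch-up of older children.

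**The concern.** The outcome is a cumulative status: a child counts as covered if all doses have ever been received, whenever that was. A child who had passed the vaccination ages before the package could act carries a largely fixed result into the endline survey. The band spans 42 months of birth cohorts, while the expected effect has only 12 to 15 months to act before endline. Much of the denominator may therefore reflect vaccination before the trial, alike in both arms apart from chance.

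Immunisation is an explicit part of the package, and the Outcome section bases the secondary outcomes on the programme's theory of change. If the definition hides a real gain in current vaccination, readers may conclude that this pathway failed. Other indicators in Table 3 are tied to current exposure, such as breastfeeding at 0–6 months and care-seeking for illness in the previous 2 weeks.

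**Working it through.** The article gives no effect size, power or sample size for vaccine coverage, so there is no figure of its own to reproduce. The check concerns how much of the denominator could respond.

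**Inputs from the article:** age band 18–59 months (18 to under 60, so 42 months wide); endline July–September 2022; effect from 1 July 2021 (Analysis) or, at the earliest, 1 January 2021 (trial start); 4480 compounds, 3 children per compound, 32 clusters.

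**Assumptions:** ages uniform over the band; completion age S = 18 months (the band's lower bound), with 15 months as an alternative; no catch-up at first.

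**Step 1. Share past 18 months when the effect starts.** With t months from onset to survey, a child aged 18 + t or more at endline was already 18 months old at onset. Share = (60 − 18 − t)/42.

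- From 1 July 2021, mid-July to mid-September 2022 (t = 12.5 to 14.5): 29.5/42 = 70% to 27.5/42 = 65%. At mid-August: 28.5/42 = 68%.
- From 1 January 2021 (t = 18.5 to 20.5): 23.5/42 = 56% to 21.5/42 = 51%.

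**Step 2. Attenuation with no catch-up.** The share still within the schedule is f = (S + t − 18)/42, and the arm difference shrinks by 1/f. Ranges run from 1 July to 30 September 2022, with mid-August in brackets.

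| Effect from | S | f | 1/f |
|---|---|---|---|
| 1 July 2021 | 18 | 0.29–0.36 (0.32) | 2.8–3.5 (3.1) |
| 1 July 2021 | 15 | 0.21–0.29 (0.25) | 3.5–4.7 (4.0) |
| 1 January 2021 | 18 | 0.43–0.50 (0.46) | 2.0–2.3 (2.2) |
| 1 January 2021 | 15 | 0.36–0.43 (0.39) | 2.3–2.8 (2.6) |

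**Step 3. Attenuation with catch-up.** Let older children gain a fraction c of what younger children gain. The signal is f + (1 − f)c. With f = 0.32:

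- c = 0.25: 0.32 + 0.17 = 0.49, attenuation about 2.0-fold.
- c = 0.5: 0.32 + 0.34 = 0.66, attenuation about 1.5-fold.

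**Step 4. Precision lost by restricting to 18–29 months.** Children per cluster: 4480 × 3/32 = 420. With uniform ages over 0–59 months, 420 × 42/60 = 294 are in the full band and 420 × 12/60 = 84 in the restricted band. Leaving aside unequal cluster sizes and compound clustering, the SE ratio is √{[(1 + 83r)/84] / [(1 + 293r)/294]}.

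- r = 0.007 (the article's mortality value): √(0.01882/0.01038) = 1.35.
- r = 0.05 (assumed): √(0.0613/0.0532) = 1.07.

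**Step 5. Break-even.** The full band has the better signal-to-noise ratio only if f + (1 − f)c exceeds 1/(SE ratio), which is 0.74 or 0.93.

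- Effect from July 2021 (f = 0.32): c above about 0.62 (r = 0.007) or 0.90 (r = 0.05).
- Effect from January 2021 (f = 0.46): c above about 0.52 or 0.87.

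**Step 6. What the restricted band contains.** Over the endline window, children aged 18–29 months were about 3 to 18 months old on 1 July 2021. All were under 18 months. With S = 15, 75–100% were still within the schedule.

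**The case against.** The strongest reply is catch-up. The outcome is ever-complete status, the package supports outreach, the Abstract describes coverage as low, and no upper age for vaccination is stated. An under-vaccinated three-year-old could become complete. Nor is there a sharp break at 18 months: a child of 16 or 17 months who missed early doses also needs catch-up. This stands, and it rules out a single dilution factor. It does not remove the attenuation unless older children gain nearly as much as younger ones.

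The July 2021 date comes from the paragraph on mortality, and vaccination could respond sooner. This stands too: counted from January 2021, the share past 18 months is nearer one half. Trial status points the other way, since by 15 September 2021 only part of the health system strengthening was in place.

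Coverage across all children aged 18–59 months is also a legitimate population quantity, and the comparison is secondary and worded as exploratory. That is a reason to keep the figure, not to make it the only test of the immunisation pathway.

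A reader might extend the point to vitamin A, which uses the same band. The article does not support that. It states two doses without a schedule age or recall period. If recent doses are asked about, every child in the band can respond, and a recall period is the kind of detail a condensed article leaves to the full protocol or questionnaire.

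**Conclusion.** The point holds for vaccine coverage. On the article's own band and dates, about 65–70% of the endline denominator was 18 months or older before an effect was expected (about 51–56% counting from January 2021). The arm difference is attenuated by roughly 2- to 5-fold without catch-up, and by perhaps 1.5- to 2-fold with moderate catch-up. The figures rest on uniform ages, a completion age of 15–18 months that the article does not state, and an unknown catch-up rate.

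A reader might take three-fold as the answer. It is the central value only with no catch-up, an 18-month completion age and a July 2021 onset, and the documents fix neither of the first two. A reader might also infer a false result. The bias is towards no difference, so it does not raise the type I error, and no power is stated from which a missed effect could be shown. The primary mortality outcome is not affected.

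**What to change.** Pre-specify the endline arm comparison of complete coverage in children aged 18–29 months, all of whom were under 18 months on 1 July 2021. Report the 18–59 month figure alongside it, labelled as population-level coverage.

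No new vaccination data are needed, because the Baseline and endline surveys section has women asked about vaccination for each under-five in their direct care. On the status the article reports (15 September 2021), endline had not begun, so the comparison could still be fixed in advance.

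The costs are a revised definition for one secondary comparison, about 84 instead of 294 children per cluster, and a standard error about 7–35% larger for the assumed intra-cluster correlations. The restricted band should not be presented as restoring the full effect: its children were already about 3 to 18 months old on 1 July 2021, so none went through the whole schedule under an expected effect. The report should say so.
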